## Abstract

**Background:**

Anthracyclines (AC), widely used and effective anticancer agents, are known to induce both acute and chronic declines in cardiovascular health, ranging in severity from asymptomatic, subclinical dysfunction to substantial cardiomyopathy leading to congestive heart failure and death. There is substantial evidence that physical activity, higher levels of cardiorespiratory fitness, and exercise therapy can help prevent cardiovascular disease. Moreover, animal studies have shown that exercise performed concomitantly with AC treatment may attenuate early cardiac damage that results from AC exposure. Our primary objective is to assess the feasibility of a 12-week aerobic exercise training (AET) program in patients receiving AC-based chemotherapy.

**Methods/design:**

This is a prospective, single-arm (pre-post-test design), feasibility study of a supervised 12-week progressive, light-to-moderate to moderate-to-vigorous intensity AET program for patients (18–65 years) receiving AC chemotherapeutic treatment for a primary/non-recurrent breast cancer or hematological malignancy. Both feasibility (e.g., participant recruitment, program adherence, safety) and intervention outcome (e.g., biological markers of cardiotoxicity, aerobic capacity, quality of life) measures will be collected. The AET program will include two, 45-min community-based exercise sessions (treadmill or cycle) per week for a total of 12 weeks. All exercise sessions will be supervised by trained exercise specialists.

**Discussion:**

Data from the EXACT study will be evaluated to determine the need to refine patient recruitment methods and general acceptability of the AET program. Preliminary data on the effects of the AET intervention on pertinent cardiac and health outcomes will also be evaluated and used to inform future studies in terms of the most appropriate outcome measure(s) to adopt and sample size estimation.

**Trial registration:**

ClinicalTrails.gov, NCT02471053

## Background

As the numbers of cancer survivors grow, the long-term adverse effects of cancer therapy are becoming increasingly apparent. Perhaps the most prominent of these are the toxic effects on the heart (cardiotoxicity) which may lead to cardiac dysfunction and increased risk of cardiovascular disease (CVD) [1]. Of note, data indicate that the magnitude of CVD risk for long-term survivors may exceed the risk of recurrent cancer and represents the leading non-cancer cause of death among survivors of breast cancer and Hodgkin’s disease [2–5]. Thus, it is clear that the long-term cardiotoxic effects of cancer therapy represent a significant concern for many cancer survivors.

While the advent of modern cancer therapies has translated into substantially improved survival, several widely used therapies have been shown to increase the risk of cardiac toxicity. Cancer therapeutics have been associated with a number of long-term cardiac complications such as decreased left ventricular function, hypertension, arrhythmias, cardiac ischemia, pericardial and valvular disease, cardiomyopathy, and congestive heart failure [6, 7]. For example, anthracyclines (AC), a chemotherapeutic agent commonly utilized in the management of many adult cancers including breast and hematological malignancies, are known to be cardiotoxic. The risk of cardiotoxicity associated with AC impacts its benefit/risk profile and ultimately limits the drugs clinical utility [6–10]. The adverse effects of AC can be associated with acute, early-onset, and chronic cardiomyocyte injury that can range in severity from asymptomatic subclinical left ventricular dysfunction to significant cardiac impairment and symptomatic heart failure [9]. Although several factors underlie the cardiotoxic effects of AC on the heart, the primary causative factor underlying acute cardiotoxicity appears to involve an inflammatory response while the formation of free radicals appears to be related to chronic AC cardiotoxicity [8] both of which can contribute to the development and progression of CVD [11–13].

The risk of developing cardiotoxicity appears to be predominately related to the total cumulative AC dose. Although the incidence of AC-induced cardiotoxicity appears to be greatest at doxorubicin dosages exceeding 700 mg/m^2^ [6, 7], cardiotoxicity has been reported in patients who have received doses as low as 100 mg/m^2^, suggesting that there is no reliably “safe” dose [14]. Specifically, the risk of heart failure has been reported in 3 to 5 % of patients that receive a cumulative dose of 400 mg/m^2^. As cumulative dose increases, so too does the incidence of heart failure. For example, at cumulative doses of 550 and 700 mg/m^2^, the incidence of heart failure has been reported as 7–26 and 18–48 %, respectively [15]. Furthermore, it has been reported that the cumulative incidence of heart failure in elderly breast cancer patients 10 years post-AC-based treatment was 38 % [15].

Patients with a pre-existing history of hypertension or CVD, those who receive AC concurrently with other known cardiotoxic agents (e.g., trastuzumab), advanced age, female gender, or those treated with mediastinal radiation are at a greater risk of developing AC-mediated CVD [8, 14]. Lifestyle factors (e.g., physical inactivity, smoking, high BMI) may also contribute to the increased risk of CVD in this population [16].

While AC cardiotoxicity is thought to cause irreversible cardiomyocyte damage (i.e., type I), recent data suggests that early detection and intervention may mitigate or reverse myocardial cell injury. Cardinale and colleagues [17] prospectively evaluated the left ventricular ejection fraction (LVEF) in 2625 AC-treated breast and non-Hodgkin lymphoma patients before, during, and after chemotherapy for a median follow-up of 5.2 years. They found that cardiotoxicity (defined as a >10 % reduction in LVEF from baseline and an end LVEF of <50 %) occurred in 9 % of patients. The majority of these cases (98 %) emerged within the first year of completing AC therapy (median time to development of cardiotoxicity was 3.5 months). Upon identification of cardiotoxicity, early heart failure therapy was initiated and full (11 %) or partial (71 %) recovery was reported in 82 % of the cases. Although this study provides data to support early detection and treatment of cardiotoxicity, challenges remain. Groarke and Nohria [18] note that the early identification of cardiotoxicity often involves the reconsideration of chemotherapy protocols resulting in either dose reductions or treatment substitutions. Given that 97 % of the reported deaths in the Cardinale et al. [17] study were cancer related, the balance of minimizing the risk of cardiotoxicity against antineoplastic efficacy becomes a significant and ongoing concern. Accordingly, intervention strategies that complement existing antineoplastic treatment strategies while decreasing the risk of cardiotoxicity are needed.

Physical activity and exercise has long been established as a powerful tool in the prevention and treatment of chronic diseases, including some cancers and CVD [19, 20]. Exercise has also been shown to reduce all-cause mortality as well as both cancer [21] and cardiovascular-related mortality [22]. Importantly, while exercise can increase aerobic fitness as well as modify traditional CVD risk factors [23], exercise may also help protect the heart from the associated cardiotoxic effects of AC-based therapy [24]. For example, several animal studies have shown that regular exercise performed prior to or concomitantly with AC treatment helps to preserve cardiac function [25–30]. Pre-treatment exercise has also been shown to decrease AC accumulation in the heart, which helps to decrease cardiotoxicity [31]. Furthermore, studies of AC-mediated cardiotoxicity have shown that regular exercise can increase antioxidant defenses [29, 32] and decrease inflammatory markers [33, 34]. These changes decrease the impact of AC-mediated oxidative stress and inflammation, thus improving myocardiocyte survival [25, 35, 36]. Thus, while much is left to be explored, exercise may prove effective in the management of AC-mediated cardiotoxicity as well as improving overall cancer survival.

Despite the increased risk of cardiotoxicity and the potential benefits of exercise therapy, the efficacy of exercise as a therapeutic intervention for the prevention of AC-mediated cardiotoxicity remains speculative. Accordingly, the purpose of this study is to examine the feasibility and potential efficacy of a 12-week, individualized aerobic exercise training (AET) program to mitigate cardiac toxicity and patient outcomes associated with AC-based chemotherapy.

The specific objectives of the study are as follows: (1) to examine feasibility outcomes (e.g., recruitment, program adherence, and safety) and (2) to explore the effects of the exercise program on biological markers of AC-mediated cardiotoxicity (e.g., levels of inflammation) as well as patient-centered outcomes (e.g., increased aerobic capacity, quality of life). We hypothesize that an individualized AET program for cancer patients receiving active AC-based treatment will be both safe and feasible with an anticipated adherence of 66–85 % [37]. We further hypothesize that the AET program will result in improvements in the overall levels of physical activity, aerobic fitness, and quality of life. Given the dearth of knowledge surrounding both the measurement of cardiac biomarkers and the cardioprotective nature of aerobic exercise in human models, no a priori hypotheses have been made. Instead, this study will serve to inform future iterations.

## Methods/design

### Study design and procedures

The protocol was drafted in accordance with the SPIRIT 2013 statement [38]. This is a single-arm, prospective (pre-post) feasibility study of a supervised 12-week light-to-moderate to moderate-to-vigorous intensity AET program. The study flow is presented for each separate cancer site in Fig. 1. Potential participants will be identified and screened for preliminary eligibility by their medical oncologist/hematologist during a regular office visit at the Queen Elizabeth II Health Sciences Center (QEII HSC) in Halifax, Nova Scotia, Canada. Pending preliminary screening for study eligibility and medical approval to participate, potential participants will be approached by a member of the medical staff to seek permission to refer them to the research coordinator to discuss the details of the study. Pending approval to be contacted by the research team, eligible participants will be provided with a detailed review of the study and informed consent will be sought by the research coordinator. Eligible participants who provide informed consent will undergo additional cardiovascular risk and fitness assessment (i.e., cardiopulmonary exercise test (CPET)) to determine study suitability and ability to safely participate in a low-to-moderate or moderate-to-vigorous aerobic training program. Those meeting the study criteria will then complete a pre-exercise baseline assessment (week 0) of anthropometric measures, select cardiac biomarkers, lifestyle behaviors, and quality of life. Based on the findings of the exercise stress test and baseline assessments, an individualized, bi-weekly AET program will be developed (weeks 1–12). Pending the completion of the 12-week training program, participants will repeat the exercise stress and cardiac function tests and the assessments measured at baseline (week 13). The study is registered with ClinicalTrails.gov (NCT02471053).

**Fig. 1 Fig1:**
[figure not shown]
Participant flow through the EXACT study representing each cancer site separately

### Setting and participants

The EXercise to prevent AnthrCycline-based Cardio-Toxicity (EXACT) feasibility study will seek to recruit 20 participants receiving active AC-based chemotherapy for either a primary breast or hematological cancer at the QEII HSC. All study assessments and exercise sessions will take place at an affiliated center located in close proximity to the cancer clinics. Potential participants will be identified based on the following inclusion criteria: (1) participants are between the ages of 18 and 65 at the time of study initiation; (2) are within 8 weeks receiving the first dose of an AC-based chemotherapeutic treatment for a primary, non-metastatic, HER2-negative breast cancer, or hematological malignancy; (3) are scheduled to receive a minimum dose of 100 mg/m^2^ of doxorubicin (or equivalent) [39]; (4) have undergone a pre-treatment cardiac function test; (5) are willing to participate in a twice-weekly, 12-week community-based AET program; and (6) have medical consent from their medical oncologist/hematologist to participate in an exercise study. Any patients that meet the inclusion criteria, but have (1) significant cognitive limitations; (2) significant cardiovascular disease (i.e., myocardial infarction, cerebrovascular disease, peripheral vascular disease, congestive heart failure, or cardiomyopathy) or any known contraindication to exercise; (3) previous history of cancer; or (4) known bone metastases will be excluded from the study.

### Intervention

In addition to standard oncologic care, all participants will be enrolled in a 12-week AET program to commence following baseline testing. Participants will be asked to complete two supervised exercise sessions on non-consecutive days each week. Session intensity will range from light-to-moderate (as defined as 35 to 55 % heart rate reserve (HRR)) or moderate-to-vigorous activity (defined as 55 to 85 % HRR). Participants will use a wrist-worn heart rate monitor (Polar Electro Canada Inc., QC) to ensure that they are training within the appropriate target heart rate zone. Exercise sessions will begin with a group warm-up activity (5 min), followed by 20–45 min of individually tailored aerobic activity (based on the maximum heart rate achieved in the absence of any clinical symptoms during the baseline CPET) and ending with a cool down (10 min). Aerobic activities will include walking on a treadmill and/or cycling on an upright or recumbent cycle ergometer. A nonlinear approach will be used to optimize adaptations to the exercise stimulus, and session intensity will be inversely related to session duration (Fig. 2) [37]. We have elected to adopt a nonlinear exercise prescription based on the foundational principles of exercise physiology, individualization, specificity, progressive overload, and recovery [37, 40, 41]. Baseline physiological testing of the target system will be measured using an incremental CPET [42]. The results of the CPET, peak workload, and peak exercise heart rate will allow for an individualized exercise prescription, rather than a generic exercise prescription based on age-predicated maximum heart rate which can result in under- or overprescription of exercise for the participant [37]. With regards to specificity, aerobic exercise was chosen to elicit cardiovascular physiological adaptations, as the purpose of the study centers around cardiotoxicity. Progressive overload will be used to guide the pattern of exercise intensity and duration over the 12-week program [40, 41]. The varied intensity between training sessions will be used to continually perturb the cardiovascular system in order to create a physiological response. However, caution will be exercised to ensure that overtraining does not occur as this could result in excessive fatigue and/or injury [37]. Thus, the exercise protocol has been designed with periods of progressive overload (either higher intensity or longer duration) with built-in periods of rest (days off) and active recovery (lower intensity, shorter duration). This type of exercise intervention has been previously utilized in oncology settings and has shown that there are favorable adherence rates (66 to 85 % adherence) and a low incidence of adverse events [37].

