
**Fig. 2 Fig2:**
[figure not shown]
Twelve-week aerobic exercise training program [37]. Note: heart rate reserve (HRR) = % of target intensity (HR_max_ − HR_rest_) + HR_rest_

To achieve a total of 150 min of light-to-moderate or moderate-to-vigorous activity each week, participants will be asked to engage in additional home-based aerobic activities (e.g., walking). Participants will be asked to keep an activity diary including a record of their resting heart rate, type of exercise performed, duration of the exercise, and maximum heart rate during all supervised and home-based exercise sessions.

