### Strategies to enhance participant recruitment, adherence, and retention

Efforts to optimize participant engagement will include on-site, face-to-face recruitment and physician endorsement. Several strategies to improve participant adherence and retention will be also be employed including group-based, individually tailored exercise training sessions; personalized performance feedback (e.g., weekly activity diary review); follow-up phone calls to inquire about missed sessions; ability to make-up missed session(s) over the course of the 12-week intervention; and scheduling flexibility.

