### Primary outcomes

#### Participant accrual, adherence, retention, and safety

The primary feasibility outcome measures for this study will include variables associated with participant recruitment, adherence, retention, and safety. Recruitment rate will be calculated by the number of patients who consent to participate divided by the number of deemed eligible to participate by their primary care oncologist/hematologist. Program adherence will be calculated by counting the actual number of sessions that the participant engaged in divided by the recommended number of weekly sessions. Participants will also be asked to record their activity duration (time) and intensity (as measured by heart rate) following each training session in order to calculate exercise volume. Participant retention will be determined by reporting the number of participants who complete baseline and post-intervention testing. Program safety will be assessed by weekly tracking and monitoring the number of adverse events or injuries that occur during the duration of the study. An investigators meeting will be held every 3 months to review and discuss all reported minor adverse events (e.g., muscle stiffness, activity-related fatigue) and injuries (e.g., muscle strain) for early risk identification and modification of study procedures as needed. All serious adverse events will be immediately disseminated to all study investigators for review and reported to the Nova Scotia Health Authority Research Ethics Board. There are currently no stopping guidelines for this trial.

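### Exercise volume in supervised sessions is calculated from participants' own records, although supervising staff and a worn heart rate monitor offer a less error-prone source

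*Protocol article*

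**What the plan says.** The source of exercise volume is set in the protocol article under Primary outcomes (Participant accrual, adherence, retention, and safety): "Participants will also be asked to record their activity duration (time) and intensity (as measured by heart rate) following each training session". The same sentence gives the purpose as the calculation of exercise volume.

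Under Intervention, after Fig. 2: "Participants will be asked to keep an activity diary including a record of their resting heart rate". The listed contents go on to type of exercise, "duration of the exercise, and maximum heart rate during all supervised and home-based exercise sessions". Supervised sessions are thus explicitly included in what participants write down.

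Three other places bear on this:

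- The abstract (Methods/design) states: "All exercise sessions will be supervised by trained exercise specialists".
- The section Intervention schedules "two supervised exercise sessions on non-consecutive days each week" and provides a wrist-worn heart rate monitor "to ensure that they are training within the appropriate target heart rate zone". No data-capture use of the monitor is stated.
- The section on strategies to enhance recruitment, adherence, and retention lists "personalized performance feedback (e.g., weekly activity diary review" among the measures to keep participants engaged.

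**The concern.** Attendance shows that a participant came. It does not show how long or how hard the participant worked. Exercise volume is the only stated measure of the dose delivered within attended sessions, and whether the planned dose can be delivered during chemotherapy is a central question for a feasibility study meant to shape a larger trial.

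For supervised sessions the article takes that measure from the participant, although a trained observer is present and a device is worn. If, as seems likely, the record is the diary reviewed each week as feedback, the document on which participants are coached is also the measuring instrument. Self-report is hard to avoid for home activity, but not for supervised sessions.

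The entry itself is also open to two readings. A participant asked for the duration of a session may give the aerobic bout or the whole visit, and the article does not say which is meant.

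**Working it through.** The article gives no figure for recording error, so there is none to reproduce. The check sets the sections side by side and then sizes what is exposed.

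**Step 1. Is self-recording stated or only inferred?** It is stated. Primary outcomes names the participant as recorder and volume as the purpose. Intervention extends the participant's diary to supervised sessions. The article mentions no staff log of duration, no monitor download and no check of entries.

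**Step 2. Is the volume record the diary?** Primary outcomes does not use the word diary. Both descriptions cover duration and heart rate for each session, so the identification is a close inference. The self-recording point does not need it; the link to weekly feedback does.

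**Step 3. How much of the dose could be recorded without self-report?** Inputs from Intervention: 2 supervised sessions a week, 20 to 45 min of aerobic work in each, and a weekly target of 150 min including home activity.

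- Supervised aerobic minutes per week: 2 × 20 = 40 to 2 × 45 = 90.
- Share of the target: 40/150 = 27 % to 90/150 = 60 %.

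**Step 4. What does the ambiguity in duration amount to?** Inputs from Intervention: 5 min warm-up and 10 min cool-down, together 15 min.

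- Whole session: 5 + 20 + 10 = 35 min to 5 + 45 + 10 = 60 min. The abstract speaks of 45-min sessions, which does not settle which duration is meant.
- Overstatement of aerobic minutes if all 15 min are counted: 15/45 = 33 % to 15/20 = 75 %.

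This assumes full counting of both phases. No section says how often, or whether, that would happen.

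**Step 5. Which planned results use volume?** Adherence is sessions attended divided by sessions recommended. The exploratory correlations under Data management and analysis relate adherence, not volume, to the secondary outcomes. No threshold for success is tied to volume. What remains exposed is the description of delivered dose.

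**Step 6. Is intensity equally exposed?** Less so, because it is read from heart rate. The remaining risk lies in choosing and copying a reading. The diary lists only the maximum heart rate during the session, and a single maximum cannot show how long a participant spent in the 35 to 55 % or 55 to 85 % heart rate reserve zone.

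**Step 7. How large is the task of recording otherwise?** 2 sessions × 12 weeks = 24 per participant; 24 × 20 participants = 480 entries at most.

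**The case against.** The strongest reply is that this is a condensed article. Session sheets, monitor downloads and checks of entries may sit in the full protocol, and their absence here proves nothing. That would answer a complaint about silence. It does not answer this point, since the article positively names the participant's record as the basis for volume, supervised sessions included.

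A second reply is that gross misreporting is unlikely: entries follow each session, staff have just watched it, heart rate comes from a monitor, and weekly review could expose implausible entries as easily as encourage convenient ones. This stands in part. It limits the likely size of the error, and it means that no direction can be claimed.

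A third reply is that a single instrument across supervised and home sessions is a defensible way to total minutes against the weekly target. This also stands, as a cost of the change.

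Finally, the ambiguity in duration is a matter of definition. A staff log would share it unless the aerobic phase is specified. That is correct, and the fix must specify it.

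**Conclusion.** The point holds in a limited form. Supervised-session volume rests on a participant record although a less error-prone source is at hand. The resulting error is avoidable, but its direction and size are unknown. The 33 % to 75 % range shows what one reading of duration would do; it does not estimate bias. The effect is confined to how delivered dose is described. The link to weekly feedback rests on the inference that the volume record is the diary.

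A reader might infer more, but the article does not support it:

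- **That errors pull volume toward the prescription.** Nothing shows this. Counting warm-up and cool-down would record a completed 45-min bout as 60 min, above the prescribed range.
- **That the error is worst in the most intense sessions.** Intensity is said to vary inversely with duration, but active-recovery sessions are described as both shorter and less intense. Fig. 2, which might settle the mix, is not shown.
- **That adherence or the planned correlations are biased.** Neither uses volume.
- **That the adverse event rate per participant hour is distorted.** The source of those hours is not stated.

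**What to change.** In Primary outcomes, state that exercise volume for supervised sessions is calculated from a log kept by the supervising specialist. The log should hold the start and stop of the aerobic phase only, excluding warm-up and cool-down, and the monitor's heart rate reading. Use the participant diary as the volume source for home sessions only, and report supervised and home volume separately, each with its source. Participants may still write down supervised sessions for feedback, as long as volume is not calculated from those entries.

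The cost is a short entry for each of up to 480 sessions, made by staff already present with equipment already worn. Because sessions are held in groups with individually tailored aerobic phases, each participant needs a separate start and stop time. Supervised and home minutes would then be measured by different instruments, so any total against the 150-min target should be shown with its two parts. Recruitment has begun, but the log can start at any session; volume recorded before that should be labelled as self-reported.
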